### Statistical analysis

The sensitivity of conventional T2w imaging is reported at 60% [21, 22]. In order to improve the diagnostic sensitivity to at least 80%, the group size calculation was based on an aimed power of 90% assuming a type I error of 5%, reaching a sample size of *n* = 114 patients.

Statistics are performed by SPSS IBM Statistics®, *p* < 0.05 will be considered statistically significant. The validity of all subjective and processed MRI measurements will be calculated using intra-class correlation coefficients (ICCs, single measures, two-way mixed effects model). The ICC values will be characterized as follows: “fair” for 0.41 to 0.6, “moderate” for 0.61 to 0.8, and “substantial” for 0.81 to 1 [23]. ICC ≤ 0.6 will not be considered acceptable.

For comparison between means, we will perform Rang-Test for independent samples. The correlation and prediction value of pathological clinical and electrophysiological factors with dynamic alterations will be calculated through multiple regression analysis. As there is no generally accepted definition of myelopathy in current literature and guidelines, we defined “functional cervical myelopathy” as presence of a relevant spinal canal stenosis in combination with mJOA-score ≤ 15 in combination with an at least mildly deteriorated SSEP of the Median nerve. By classification of our patients into two groups (functional present or abstinent myelopathy), we will be able to determine the sensitivity and specificity of the new imaging procedure.

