**Methods:**

A monocentric, prospective longitudinal observational trial on cervical spinal canal stenosis will be conducted at the University Medical Center Freiburg. Patients (*n* = 130) with relevant cervical spinal canal stenosis, being defined by at least contact to the spinal cord, will be included. Also, we will examine a control group of healthy volunteers (*n* = 20) as proof-of-principle. We will observe two openly assigned branches of participants undergoing conservative and surgical decompressive treatment (based on current German Guidelines) over a time course of 12 month, including a total of 4 visits. We will conduct a broad assessment of clinical parameters, standard scores and gradings, electrophysiological measurements, standard MRI, and adapted functional PC-MRI of spinal cord motion. Primary endpoint is the evaluation of an expected negative correlation of absolute spinal cord displacement to clinical impairment. Secondary endpoints are the evaluation of positive correlation of increased absolute spinal cord displacement to prolonged evoked potentials, prediction of clinical course by absolute spinal cord displacement, and demonstration of normalized spinal cord motion after decompressive surgery.

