## Methods

### Aim of the study

The results of this study should provide a new and reliable diagnostic tool in the field of cervical spinal canal stenosis by the use of adapted PC-MRI. The additional dynamic data of spinal cord motion should be demonstrated to be clinically relevant.

Primary endpoint is the evaluation of the expected negative correlation of absolute spinal cord displacement to clinical impairment. Secondary endpoints are assessments of expected positive correlation of increased absolute spinal cord displacement to prolonged evoked potentials, prediction of clinical course in spinal canal stenosis by absolute spinal cord displacement, demonstration of reduced spinal cord motion after decompressive surgery and comparison of standard MRI-techniques with PC-MRI.

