### Design

This study is an investigator initiated prospective, longitudinal, monocentric observational trial. The trial consists of two openly assigned treatment branches: conservative treatment and surgical decompressive treatment.

The study protocol has been approved by the institutional ethics committee of the University of Freiburg, Germany (reference number 261/17). The trial was registered at the German Clinical Trials Register (DRKS00012962) on January 17, 2018. The study-population is linked to another trial at our center (MIDICAM trial). The screening period started in April 2018.

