### Time-line and study protocol

After enrolment within the study and primary visit (t0, including standardized neurological and electrophysiological assessments) patients will be assigned to conservative or surgical treatment (Fig. 1) based on German Guidelines [13]. The assignment will be conducted by study-independent neurosurgeons and neurologists of the University Medical Center Freiburg who are blinded to the PC-MRI results but will consider clinical and electrophysiological findings of the first visit. In case of not given consent to recommended surgery, patients will still receive follow-up visits according to the study protocol but will be indexed as assigned to the surgical treatment branch and statistically analyzed as a subgroup. All patients will receive clinical follow-up visits at 3 (t1), 6 (t2), and 12 (t3) months. At the primary visit (t0) and at 12 month (t3), all patients will undergo MRI assessments, expanded clinical assessments, and additional electrophysiological diagnostics.

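### The only test named for comparing means is for independent samples, but the post-surgery secondary endpoint compares t0 and t3 in the same patients

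*Protocol article*

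**What the plan says.** The Statistical analysis section gives one rule for comparing means: "For comparison between means, we will perform Rang-Test for independent samples". The sentence is not tied to any endpoint or pair of groups. The other method for relating outcomes to cord motion is regression: "The correlation and prediction value of pathological clinical and electrophysiological factors with dynamic alterations will be calculated through multiple regression analysis". No paired or repeated-measures test appears in the article.

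The Aim of the study section lists "demonstration of reduced spinal cord motion after decompressive surgery" among the secondary endpoints. The Methods paragraph of the Abstract words the same endpoint as "demonstration of normalized spinal cord motion after decompressive surgery". On timing, the Time-line and study protocol section says: "At the primary visit (t0) and at 12 month (t3), all patients will undergo MRI assessments". The Design section adds: "The trial consists of two openly assigned treatment branches: conservative treatment and surgical decompressive treatment". The size of the surgical branch is not stated.

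**The concern.** Whether motion falls after decompression is a before-after question. Each operated patient supplies one displacement value at t0 and one at t3, and the two are likely to be positively correlated. A rank test for independent samples treats them as coming from different people, so it uses too large a variance for the difference. Its p-values are then too large, and a real reduction is more easily missed.

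The endpoint's two wordings make the intended comparison less clear. *Reduced* points to t3 against t0 in the same patients. *Normalized* points naturally to operated patients against the 20 healthy controls. These are different contrasts, need different tests and set different criteria for success.

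**Working it through.** **The plan's own figure.** The article's only sample-size figure, 114 patients, is for raising diagnostic sensitivity from 60% to 80% with 90% power and 5% type I error. A two-sided McNemar calculation, with the two imaging methods assumed independent within patients (discordant cells 0.8 × 0.4 = 0.32 and 0.2 × 0.6 = 0.12, sum 0.44, difference 0.20), gives n = (1.96·√0.44 + 1.282·√(0.44 − 0.04))² / 0.04 = 111.4, so 112, close to 114. It says nothing about the post-surgery endpoint, for which the article gives no power calculation.

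**Inputs for the post-surgery endpoint.** From the article: the test (independent-samples rank test), measurement at t0 and t3 in the same patients, and a 5% significance level. Assumed, because the article does not give them: the number operated n, the standardised change d, the t0–t3 correlation ρ, normal data with equal variances, and two-sided testing.

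**Type I error, by approximation.** With SD 1, the true variance of the mean difference is 2(1 − ρ)/n. An independent-samples test works with 2/n, so its effective critical value is 1.96/√(1 − ρ):

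- ρ = 0.3: 1.96/√0.7 = 2.34, two-sided error about 1.9%
- ρ = 0.5: 1.96/√0.5 = 2.77, about 0.6%
- ρ = 0.7: 1.96/√0.3 = 3.58, about 0.03%

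**Power, by approximation**, for n = 50 and d = 0.4. The signal is d·√(n/2) = 0.4 × 5 = 2.0. Power is Φ((2.0 − 1.96)/√(1 − ρ)) for the independent test and Φ(2.0/√(1 − ρ) − 1.96) for the paired test. At ρ = 0.5 these are Φ(0.06) = 52% and Φ(0.87) = 81%. Rank tests give up a little of this.

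**Simulation of the rank tests themselves**, n = 50 operated, d = 0.4:

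| ρ | Independent rank test, power | Signed-rank test, power | Independent test, actual type I error |
|---|---|---|---|
| 0 | 50% | 49% | about 5% |
| 0.3 | 49% | 63% | 2.3% |
| 0.5 | 50% | 77% | 0.8% |
| 0.7 | 48% | 94% | 0.05% |

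The signed-rank test stays at about 5% type I error throughout. The losses are 63 − 49 = 14 points at ρ = 0.3, 77 − 50 = 27 at ρ = 0.5 and 94 − 48 = 46 at ρ = 0.7.

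**Other assumed settings** (independent v signed-rank):

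- n = 30, d = 0.5: 44% v 58% at ρ = 0.3; 45% v 74% at ρ = 0.5
- n = 65, d = 0.3: 36% v 50% at ρ = 0.3; 33% v 64% at ρ = 0.5
- n = 65, d = 0.5, ρ = 0.5: 86% v 97%
- n = 30, d = 0.8, ρ = 0.5: 91% v 98%
- n = 50, d = 0.8: 98.5% v 99.6% at ρ = 0.3; 99.7% v 99.9% at ρ = 0.5

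**The case against.** The strongest reply is that the article never assigns the independent-samples test to the t0–t3 contrast. The design has several comparisons for which that test is right: patients against controls, surgical against conservative, myelopathy present against absent, and change scores between the branches. The article is condensed, and an analysis plan that is not shown may name a paired test. This stands in part: misuse is a consequence of following the sentence as written, not something the article announces. But the sentence is an unrestricted rule, and it does not fit one of the listed endpoints. A plan with a paired test would have to depart from it.

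A second reply is that the loss of power rests on assumptions and may be small. That stands. The Discussion reports earlier displacement at the stenosis of up to twofold or more relative to C2. This gives no SD, but a large effect is plausible, and at 0.8 SD with 50 operated the two tests hardly differ.

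Three stronger readings are tempting and are not supported:

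- **The error could produce false claims of benefit.** With positive correlation it works the other way: the test rejects too rarely.
- **The stenosis-level against C2 comparison is also mis-tested.** It is not a listed endpoint, and the MRI section derives a cranio-caudal ratio, which plausibly gives one value per patient and so already absorbs the pairing.
- **The trial will declare motion normal from a non-significant comparison with 20 controls.** No passage says so; the controls are described as a proof-of-principle group. If *normalized* does mean a comparison with controls, an independent-samples test is the right kind.

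**Conclusion.** The point holds in limited form. The one test named for comparing means does not suit the within-patient endpoint of reduced motion after surgery. Used there, it is conservative, with actual type I error of about 2% at ρ = 0.3 and under 1% at ρ = 0.5. The calibration result depends mainly on ρ. The power loss also depends on the number operated and the effect size, neither of which the article gives; it ranges from nothing to a substantial share.

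Severity is modest. A reader might infer that the main result or the sample size is compromised, but the primary endpoint is a correlation, and the figure of 114 concerns diagnostic sensitivity. The difference between *reduced* and *normalized* is a separate inconsistency of wording that should be settled at the same time.

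**What to change.** In Statistical analysis, state that the t3 minus t0 change in displacement among patients who were operated on will be tested with the Wilcoxon signed-rank test, or estimated in a mixed model. Specifying operated patients matters because the Time-line section indexes those who decline recommended surgery to the surgical branch. Restrict the independent-samples rank test to between-group contrasts: patients v controls, surgical v conservative, myelopathy present v absent.

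Use one wording for the endpoint in the Abstract and in the Aim of the study. If *normalized* is kept, report the difference between operated patients at t3 and controls with a 95% confidence interval.

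The cost is one or two sentences in the analysis section and one word in the Abstract. No visit, scan or patient is added, and the change can be made at any time before analysis.

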## Discussion

In cervical spinal canal stenosis, the deterioration of the spinal cord is caused by several mechanisms related to loss of blood-supply leading to neurotoxic effects beginning within the central gray matter and later affecting the entire spinal cord segment [24]. Mostly, these mechanisms are attributed to the increasing pressure on the spinal cord and the subarachnoid vessels [24].

With application of PC-MRI, oscillations of the spinal cord in healthy conditions have been noted within several studies (e.g., [25–27]). In physiological conditions, the origin of spinal cord motion could be attributed to pulsatile impact of local arteries [28, 29] as well as effects related to breathing and brain movements, that itself derives from arterial in- and venous outflow [27]. The data of a pre-study indicated a positive correlation of spinal cord motion to age within healthy conditions but needs further evaluation [10]. Spinal cord motion in the non-comprised cervical spinal canal was at about 0.5–0.6 cm/s; intraindividually, there were only minor differences of spinal cord motion between cranio-caudal segments (index C2/C5 about 1) (e.g., [10]).

Within cervical spinal canal stenosis, three studies independently demonstrated that spinal cord motion at level of stenosis is significantly increased patients. Interestingly, the intraindividual difference of the total displacement (=area under the curve, or absolute spinal cord motion) at level of stenosis C5 was significantly increased compared to the intraindividual spinal cord motion at C2 up to a twofold or higher, pointing towards a local dynamic impact on the spinal cord [10]. Interrater-reliability of this method was higher than 90%, the method itself uses conventional PC-MRI sequences and is timely feasible [10].

Focusing on the dynamics of the spinal cord comprises two benefits in contrast to a so far mostly favored analysis of CSF-alterations: first, the affected CNS and its mechanical stress is much more likely to be directly linked to functional impairments other than being an epiphenomenon. Second, the spinal cord resembles a solid structure that can be easily assessed without any short distance alterations requiring tremendously high spatial resolution MRI and therefore a more complex and time-consuming acquisitions.

It has been discussed, whether the observed increased spinal cord motion measured by PC-MRI is an artifact of interstitial cell fluids or CSF-flow [12]. We do not share this assumption due to two facts: First, the spinal cord can be delineated from surrounding CSF (see also Fig. 2) so that a systematic error of the measured spinal cord velocities because of effects from CSF flow can be minimized by careful selection of a region of interest. This is supported by a high interrater-reliability as demonstrated with the pre-study [10]. Second, the measured mean velocity and associated total displacement values of up to 5–6 mm per heart beat within cranio-caudal direction over a region of almost 20 mm^2^ [10] are substantially larger as would be expected because of interstitial fluid flows.

This will be the first longitudinal clinical study on spinal cord motion in cervical spinal canal stenosis and its diagnostic value on functional impairment and clinical course.

### Limitations

Limits of the study are non-randomized design and in parts non-blinded analysis and acquisition of the data. Still, in order to demonstrate the objectivity of this analysis, we will provide sufficient proof of interrater-reliability by analysis of the MRI-datasets by two independent researchers.

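### Agreement between two readers is offered as proof of objectivity for a partly non-blinded PC-MRI analysis, but it cannot exclude a bias that both readers share

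*Protocol article*

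**What the plan says.** The Limitations section concedes the weakness: "Limits of the study are non-randomized design and in parts non-blinded analysis and acquisition of the data". The next sentence offers the remedy: "Still, in order to demonstrate the objectivity of this analysis, we will provide sufficient proof of interrater-reliability", to be obtained "by analysis of the MRI-datasets by two independent researchers". It does not say which steps of analysis or acquisition are unblinded.

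Two other places also rest on reader agreement. Under Statistical analysis the coefficient is presented as a measure of validity: "The validity of all subjective and processed MRI measurements will be calculated using intra-class correlation coefficients (ICCs, single measures, two-way mixed effects model", with the acceptance rule "ICC ≤ 0.6 will not be considered acceptable". In the Discussion, systematic error in cord velocity from CSF flow "can be minimized by careful selection of a region of interest", and the high inter-rater reliability of the pre-study is cited in support.

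Blinding is stated in one direction only. Those who assign treatment (Time-line and study protocol) and those who perform the clinical assessments (Clinical parameters) do not know the PC-MRI results. The article states no masking of the PC-MRI readers to clinical findings, treatment branch or visit.

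**The concern.** The primary endpoint correlates absolute cord displacement with clinical impairment, and the expected direction is declared in advance. Displacement is computed from velocities inside a region of interest, and the article itself says that selecting this region needs care. If the person selecting it knows how impaired the patient is, or that the scan follows decompression, the choice can drift towards the expected result.

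A second reader with the same knowledge may drift the same way. Being independent of each other does not make two readers blind to the patient's status. The ICC compares readers with each other and not with the truth, so it does not register a drift they have in common. The safeguard named in the article therefore does not address the weakness it is offered against. At stake are the primary correlation and the secondary claim that motion falls after surgery.

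**Working it through.** The plan states no figure for this point, so there is none to reproduce. The check asks whether a shared bias would show in the ICC.

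**Inputs from the article.** There are two readers (Limitations) and 130 patients (Study population). The pre-study's inter-rater reliability was above 90% (Discussion); I take this as an ICC of 0.90, although the article does not say that it is one.

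**Assumed input.** The shared bias is b SD of displacement per SD of impairment, shown at 0, 0.25 and 0.5. The article gives no value.

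**Model.** Reader j's value for patient i is x_ij = t_i + b·c_i + e_ij. Here t is true displacement (variance 1), c is impairment (variance 1, independent of t, so the true correlation is 0), and e is reader error. Setting Var(e) = 1/9 gives ICC = 1/(1 + 1/9) = 0.90 when b = 0.

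**Formulas.**
- ICC = (1 + b²)/(1 + b² + 1/9). The shared bias enters as if it were genuine variation between patients.
- Correlation of the two-reader mean with impairment = b/√(1 + b² + 1/18).

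**Numbers.**
- b = 0.25: ICC = 1.0625/1.1736 = 0.905; correlation = 0.25/√1.1181 = 0.236.
- b = 0.5: ICC = 1.25/1.3611 = 0.918; correlation = 0.5/√1.3056 = 0.438.

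A simulation of 2,000 trials with n = 130 agrees:

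| Assumed b | Mean ICC | Mean correlation (absolute) | Significant at two-sided 5% |
|---|---|---|---|
| 0 | 0.90 | 0.00 | 5% |
| 0.25 | 0.90 | 0.23 | 77% |
| 0.5 | 0.92 | 0.44 | over 99% |

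The ICC does not fall as the false correlation grows; it rises slightly. All three rows pass the plan's limit of 0.6 and would be labelled substantial. The consistency and absolute-agreement forms of the ICC gave the same values in these runs, so choosing the other form would not reveal the problem.

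**Comparison after surgery.** If both readers shift a patient's 12-month value by the same amount m because they know surgery has taken place, the change from baseline shifts by m. The difference between the readers is unchanged, because m cancels from it.

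**The case against.** The strongest reply is that the weakness is disclosed and that the article is a condensed text. Details of reader masking may sit in a fuller document that is not shown. The clinical side of the correlation is protected, because assessors and treatment assigners do not see PC-MRI results. Displacement is an area under a measured velocity-time curve in a structure that the article describes as solid and easily assessed, and nothing in the article shows that region selection can move it materially. The bias values in the working are assumed.

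Most of this stands, and it limits the point in two ways. First, a reader might infer that the PC-MRI readers do know the clinical scores, or that the primary correlation will be inflated. The article supports neither: it says only that parts are unblinded, and it gives no size. Second, the reply does not rescue the inference actually made in the Limitations section. That section admits non-blinded analysis and then names agreement as the demonstration of objectivity, which is a stated argument and not a detail left for elsewhere.

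A reader might also infer that the planned ICC hides a constant offset between readers. A two-way mixed ICC does so only in its consistency form. The article names neither form, and that choice is ordinary analysis-plan detail. The sizes are also assumed and depend on the scale. With a consistency ICC of 0.90 and an offset of 1 SD, absolute agreement is 0.9/(0.9 + 0.1 + 0.5) = 0.60 in total-SD units, but 1/(1 + 1/9 + 0.5) = 0.62 in between-patient SD units. The first meets the plan's rejection rule and the second does not. A constant offset also leaves the primary correlation unchanged if one reader, or the mean of both, is used throughout. Kappa for the yes/no T2w sign is likewise optional and concerns a measure that is not primary.

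**Conclusion.** The point holds in a narrow form. Reader agreement is evidence of reproducibility. It cannot show that a partly non-blinded reading is objective or valid, because a bias common to both readers leaves the ICC where it was or raises it slightly. Such a bias would act on the primary correlation and on the comparison after surgery.

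Whether it is present, and how large it would be, cannot be computed from the document. The values for b = 0.25 and 0.5 show the mechanism under an assumed bias, normal data, no true correlation and a starting ICC of 0.90; they do not estimate what will happen in this trial. The conclusion that the ICC is blind to a shared bias does not depend on the value of b. The form of the ICC and the use of kappa are not part of the error. The point warrants a change because the remedy is cheap and bears on the primary measure.

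**What to change.** 1. Have the two existing researchers process pseudonymised PC-MRI data sets in random order, without mJOA, SSEP or MEP grade, treatment branch or, where possible, visit label.
2. Lock the displacement values before they are linked to clinical data.
3. State which steps of acquisition and analysis remain unblinded.
4. In Limitations and Statistical analysis, describe the ICC as evidence of reliability, and remove the claims that it shows objectivity or validity.

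Stating the ICC form, or using kappa for the T2w sign, may be added but is optional.

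The cost is the work of pseudonymising and ordering files, plus a few lines of text; no extra reader is needed. Masking will be incomplete at 12 months where surgical change is visible, the severity of stenosis can be seen in the images themselves, and acquisition may stay unmasked. The baseline reading, which can supply the primary correlation, can still be masked to clinical and electrophysiological scores.
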